### Participants and eligibility criteria

Male students from the first, second, third and fourth grades will be invited to participate in the study. Those with overweight or obesity, defined as a measured Body Mass Index (BMI) equal to or greater than 25 kg∙m^-2^ [20] and a percentage of body fat (%BF) equal to or greater than 21%, evaluated by bioelectrical impedance [21] will be enrolled. Exclusion criteria are: (1) reported diabetes mellitus or cardiovascular diseases and (2) musculoskeletal injuries or any other factor that precludes the achievement of the exercise protocol.

### Intervention and exercise protocol

For students willing to participate in the study, an exercise treadmill test will be performed prior to the intervention sessions in order to evaluate clinical symptoms and physiological responses during exercise.

The intervention groups (MEG and VEG) will be submitted to exercise sessions in the evening (5–7 p.m.), performed three times a week (Monday, Wednesday and Friday) for 65 min, during a 2-week period. Exercise intensity will be set according to the oxygen uptake reserve (VO_2_R) concept, calculated considering the peak oxygen consumption directly measured during an incremental treadmill test.

Physical exercise sessions will be divided into three phases: warm-up (5 min), training (55 min) and cool-down (5 min). During warm-up and cool-down phases, for both the MEG and the VEG, participants will be instructed to walk at a low intensity.

The training phase of the MEG will consist of four sets of 10 min of walking/running at moderate intensity (40 to 59% VO_2_R), with 5 min walking at low intensity (30 to 39% VO_2_R) for recovery between sets [22]. The training phase of the vigorous exercise group (VEG) will consist of four sets of 10 min of running at vigorous intensity (60 to 89% VO_2_R), with 5 min of walking at low intensity (30 to 39% VO_2_R) for recovery between sets [22].

Participants will self-monitor their target heart rate using a heart-rate monitor Polar FT1 (Polar Electro Oy, Kempele, Finland). In addition, the researchers will monitor all physical exercise sessions to ensure that they will perform the experimental protocol properly.

Participants in the CG will not be submitted to any specific physical training protocol. No specific counseling to change the daily routine of participants during the 15 days will be provided.

### Sample size

Sample size was calculated based on a mean difference in daily energy expenditure between groups of 110 kcal [23], with a coefficient of variation equal to 1 (standard deviation of 110 kcal) [24]. The sample size required for the study, with an *α* of 0.05 (two-sided), *β* of 0.10 and estimating a drop out of 20%, is 81 adolescents (i.e., 27 in each group) [25].

### Randomization and allocation concealment

Eighty-one participants will be randomly allocated into three groups in a 1:1:1 ratio. The randomization list will be generated in blocks and the allocation sequence will be concealed using opaque envelopes by a researcher not involved in recruitment. Block size will be blinded from investigators involved in patients’ recruitment.

### Blinding

Participants and physical trainer blinding will not be feasible due to the characteristics of prescribed exercise sessions. However, the evaluators will be blinded to the following endpoints: weight, body composition, appetite, energy intake and laboratorial biomarkers.

### Outcomes

The primary outcome will be total physical activity energy expenditure during the 2-week period. Secondary outcomes will be caloric intake, hungry and satiety sensations and biomarkers (lactate, cortisol, insulin, leptin, acylated ghrelin).

### Measurements

#### Anthropometric

Body weight will be measured using a portable electronic scale (Tanita BC-558 Japan) with a 150-kg capacity and 50-g precision, with minimal clothing and without shoes. Height will be measured using a portable stadiometer (Alturexata, Brazil) with an amplitude of 200 cm and variation of 0.1 cm. Body Mass Index will be determined as a ratio between body weight (kg) and squared height (m).

#### Body composition

Body composition will be estimated by tetrapolar bioimpedance analysis (BIA), model RJL System, according to the standard tetrapolar technique [26–28]. The electrodes will be placed at the dominant wrist and ankle. Fat-free mass (FFM) and body fat (BF) will be calculated from impedance (resistance and reactance) and anthropometry (body weight and height) data, according to RJL software parameters.

In order to obtain accurate measurements, a standardized procedure will be followed: (1) light clothes, without shoes or socks; (2) supine position for 5–10 min before measurements; (3) no eating or drinking within 4 h of the test; (4) no alcohol consumption within 12 h of the test; (5) no exercise within 8 h of the test; and (6) urinate within 30 min of the test [29].

#### Exercise treadmill testing

In order to evaluate clinical symptoms and physiological responses during exercise, a blinded exercise physiologist will perform a standard ramp protocol on a treadmill, Master Super ATL model (Inbramed, Porto Alegre, RS, Brazil).

The test will start at 8 km∙h^-1^ with 1% inclination and will continue with an increase ratio of 0.8 km∙h^-1^∙min^-1^ until exhaustion/interruption request or the observation of some criterion indicating the interruption. Ventilatory variables, blood gases and heart rate (HR) will be monitored and recorded through a MedGraphics VO2000® (Medical Graphics Corporation, Saint Paul, MN, USA) metabolic analyzer, connected to a Polar® heart-rate monitor (Polar Electro Oy, Kempele, Finland). The maximum oxygen consumption or peak oxygen consumption (VO_2_max or VO_2_peak), maximum heart rate (HRmax), total test time, perceived exertion rate (Borg scale from 0 to 10) [30] and the reason for the test interruption will be obtained from the test. In addition, through visual inspection analysis, by consensus of two experienced evaluators, ventilatory thresholds 1 and 2 will be identified. For these thresholds, the oxygen consumption in which they are observed and the HR in these stages will be recorded for prescription decisions.

The test will be interrupted according to the following criteria: fall in the variables minute ventilation (VE), oxygen consumption (VO_2_) or oxygen pulse (VO_2_∙beat^-1^) with increased load, claudication, severe headache, chest pain or patient’s inability to continue the test. The test will be considered maximum if at least one of these criteria is achieved: plateau in VO_2_, percentage of HRmax (% HRmax) predicted for age (220 − age) close to or greater than 100%, respiratory quotient (CO_2_/O_2_) greater than 1.15, rate of perceived exertion close to 10 and observation of the two ventilatory thresholds.

#### Physical activity energy expenditure

Physical activity energy expenditure will be assessed for all groups (control, MEG and VEG) by using triaxial accelerometers (ActiGraph GT3x-BT, Pensacola, FL, USA) [31]. The device will be positioned at the anterior axillary line of the non-dominant hip, for 15 consecutive days. Participants will be instructed to not remove the device during this period, except for bathing and water-based activities.

Accelerometers will be initialized to collect data in 30-Hz time resolution and in 5-s epochs. Non-wear time will be defined as ≥ 60 min of zero counts, with a minimum of 10 h constituting a valid day. Therefore, individuals will have days excluded from the analysis if they failed to provide a minimum of 600 min (10 h) of valid data.

The recorded data from the accelerometer in form of counts will be analyzed using the ActiLife 6 software (ActiGraph Manufacturing Technology Inc., FL, USA). Physical activity energy expenditure will be calculate based on equations proposed by Santos-Lozano et al. [32], which presented for adults a coefficient of determination (R^2^) of 0.71 (standard error of the estimation of 1.21 and root mean sum of squared errors of 1.20).

#### Food consumption

Food and beverage consumption will be assessed by 24-h food recalls (REC24h). Nutritionists will conduct a face-to-face interview in four different moments during the intervention period: on the second and fifth days (Tuesday and Friday) in the first week; and at the 11th and 15th days (Thursday and Monday) in the second week. These days were selected to encompass weekdays (second, fifth, 11th) and weekend (15th), and days with (second, 11th) and without (fifth, 15th) exercise session.

During the interviews, each participant will be asked to report all food and beverages consumed (except water) on the previous day, including a description of food items, the amount consumed and the time of consumption. All items at each meal will be reviewed to ensure that no item is omitted, according to the menu at the restaurant. The 24-h recalls will be analyzed using the BrasilNutri software that encompasses a computerized food database developed for the 2008–2009 nationwide dietary survey [33].

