**Methods:**

This study is a randomized controlled trial with parallel, three-group experimental arms. Eighty-one overweight/obese adults will be randomly allocated (1:1:1 ratio) to a vigorous exercise group, moderate exercise group or control group. The trial will be conducted at a military institution and the intervention groups will be submitted to exercise sessions in the evening, three times a week for 65 min, during a 2-week period. The primary outcome will be total spontaneous physical activity energy expenditure during a 2-week period. Secondary outcomes will be caloric intake, appetite sensations and laboratorial biomarkers. Intention-to-treat analysis will be performed using linear mixed-effects models to evaluate the effect of treatment-by-time interaction on primary and secondary outcomes. Data analysis will be performed using SAS 9.3 and statistical significance will be set at *p* < 0.05.

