### Study setting

The trial will be conducted at the Naval Academy (Brazilian Navy, Rio de Janeiro, Brazil) during the school year of 2017. This military academic institution allows a very controlled experimental condition to conduct this study. In this institution, approximately 900 students, aged 18 to 24 years, undergo a military training during a period of 4 years. The institution works on boarding from Monday to Friday and during the weekend students are free to go home.

During the weekdays, all students have the same routine at school: they wake up at 6 a.m., attend academic classes in the morning and physical exercise classes in the afternoon. The school offers three basic meals: breakfast at 6 a.m., lunch at 12 p.m. and dinner at 7 p.m. At 10 p.m. students must go to their bedrooms to sleep.

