**Fig. 3 Fig3:**
[figure not shown]
Visual analog scale of hunger and satiety sensations

Prior to the first exercise session, an ad-libitum buffet will be provided to all experimental groups (vigorous, moderate and control).

Participants will be asked to record hunger and satiety sensations in a diary. In order to improve adherence, a text message will be sent to the participants reminding them to complete their diary.

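### Testing caloric intake by treatment-by-time on four recalls of differing day type can turn a steady arm effect into a trend, or miss it; day-type contrasts on the same interview days avoid this

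*Protocol article*

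**What the plan says.** Under Food consumption, nutritionists interview each participant "on the second and fifth days (Tuesday and Friday) in the first week; and at the 11th and 15th days (Thursday and Monday) in the" week that follows. Participants "report all food and beverages consumed (except water) on the previous day". The section says the days were chosen to cover "weekdays (second, fifth, 11th) and weekend (15th), and days with (second, 11th) and without (fifth, 15th) exercise session".

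Under Intervention and exercise protocol, sessions fall on Monday, Wednesday and Friday between 5 and 7 p.m. Study setting adds: "The institution works on boarding from Monday to Friday and during the weekend students are free to go home". The text with Fig. 3 adds: "Prior to the first exercise session, an ad-libitum buffet will be provided to all experimental groups (vigorous, moderate and control"), without giving its date.

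The abstract plans "linear mixed-effects models to evaluate the effect of treatment-by-time interaction on primary and secondary outcomes". Outcomes lists caloric intake as secondary, although the primary objective names energy intake beside energy expenditure. Data analysis describes the treatment-by-time term as giving a rate of change. Neither place names a day-type or weekend term for intake.

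**The concern.** The recalls were chosen to sample different kinds of day, but the stated test reads their order as elapsed time. The only weekend day is also the last time point, and it is the only recalled day on which students may be away from the school. The first recall covers the day of the first session, when breakfast and lunch come before any exercise. No pre-intervention recall is described, so there is no clean starting level from which a rate of change would run.

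The question of interest is whether exercise alters intake. The Discussion raises reduced intake after high-intensity exercise as one possible mechanism, while noting that findings conflict. Such an effect belongs to session days and need not grow or shrink over two weeks. A treatment-by-time slope could report a steady effect as a decline or an increase, or not see it at all, and the result could then be taken for adaptation.

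**Working it through.** The documents give no expected effect or SD for intake, so there is no planned figure to reproduce. The calendar can be checked first.

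**Recalled days.** Day 2 is a Tuesday, so day 1 is a Monday. Recalled day = interview day − 1.

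| Interview | Recalled day | Session | Weekend |
|---|---|---|---|
| Day 2, Tuesday | Day 1, Monday | yes | no |
| Day 5, Friday | Day 4, Thursday | no | no |
| Day 11, Thursday | Day 10, Wednesday | yes | no |
| Day 15, Monday | Day 14, Sunday | no | yes |

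This agrees with the protocol's own labels.

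**Slope of the between-arm difference.** With t = 1, 4, 10, 14, the mean is 29/4 = 7.25. The deviations are −6.25, −3.25, 2.75 and 6.75, and their sum of squares is 102.75. For a between-arm difference with pattern e, the slope is Σ(deviation × e)/102.75 per day, multiplied by 13 for the span from day 1 to day 14. This equals the group-by-time slope of a mixed model with linear time, a random intercept and complete data.

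| Arm difference D | Slope per day | Over 13 days |
|---|---|---|
| Session days only (1,0,1,0) | (−6.25 + 2.75)/102.75 = −0.0341 D | −0.44 D |
| Sunday only (0,0,0,1) | 6.75/102.75 = +0.0657 D | +0.85 D |
| Equal on all four days (1,1,1,1) | 0 | 0 |

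Coding the occasions 1 to 4 instead gives −0.60 D for the session-day pattern and +0.90 D for Sunday.

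**When the sign reverses.** If day 1 carries a fraction f of the session-day effect, the numerator is 2.75 − 6.25f. It is negative only if f > 2.75/6.25 = 0.44. With f = 0 the trend is 2.75 × 13/102.75 = +0.35 D.

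**What can be separated.** Each week has one session day and one non-session day. A session-day effect therefore adds D/2 to each week's mean, and the week contrast is D/2 − D/2 = 0. Adding a session-day term to linear time raises the slope variance only 1.14 times. Adding session-day and Sunday terms, each by arm, gives four mean parameters per arm for four occasions. The slope is then (day 10 − day 1)/9, with variance (2/81) × 102.75 = 2.54 times that of the plain slope.

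**Illustrative size, on assumed values.** Assume a within-person SD of 400 to 800 kcal, 22 to 27 per arm, and D of 100 to 400 kcal carried in full on both session days. The artefact is 0.0341 × D = 3.4 to 13.6 kcal per day. The standard error of the slope difference, SD × √(2/(n × 102.75)), is 10.7 to 23.8 kcal per day. The chance of a significant slope of the wrong sign is 3.5% to 24.5%, against 2.5% with no artefact.

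**The case against.** Much of the case on the other side stands.

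- A reader might infer that session effects and time cannot be told apart here. They can: session status is balanced across the two weeks. Only the Sunday effect is strongly tied to time.
- A reader might infer that the slope always has the wrong sign. It does so only for a session-day effect of which day 1 carries more than 44%. Treating day 1 as almost free of exercise effect and also claiming a full −0.44 D would be inconsistent.
- An effect absent on day 1 and present on the other three recalls gives (−3.25 + 2.75 + 6.75) × 13/102.75 = +0.79 D. That is a genuine change over time, correctly signed, and not an artefact.
- Day-type effects shared by all arms cancel in the interaction. The buffet goes to every arm, so it matters only if its effect differs by arm. That it falls on day 1, or that students eat at home on Sunday, is inference: the protocol does not date the buffet and says only that students are free to go home.
- Linear time for intake is itself inferred. The rate-of-change sentence follows text on energy expenditure, and the abstract says only treatment-by-time. Categorical time would remove the linear artefact, but the interaction would still mix day type with time.
- Time coding and covariates may be settled in a fuller plan that is not shown. Even so, full day-type adjustment of the slope leaves it resting on days 1 and 10 alone.

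What remains is that the stated test for intake does not suit the days the protocol fixes.

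**Conclusion.** The point holds as a mismatch between fixed recall days and the stated test, for a secondary outcome that is also named in the primary objective. With linear time, a steady session-day arm effect is read as −0.44 D over 13 days (given f > 0.44), a Sunday-only arm effect as +0.85 D, and an equal effect on all days as no effect. These multiples follow from the calendar and the linear-time reading; the kcal figures and probabilities rest on assumed values. The primary outcome and the sample size are untouched. The documents do not support the stronger reading that the recall schedule is unusable or must be moved.

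**What to change.** Keep the four interview days. For intake, replace the treatment-by-time slope with a mixed model containing arm, day type (session weekday, rest weekday, Sunday) and arm × day type. Name two sets of effects:

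1. The between-arm difference averaged over the four recalls. An equal effect D on all days gives D, and a session-day effect gives D/2 with the right sign.
2. The between-arm difference by day type, with session versus rest compared on weekdays only and Sunday reported separately.

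Add a sensitivity analysis without day 1, because breakfast and lunch that day precede any session and the buffet may fall on it. State the buffet's date. Do not interpret a treatment-by-time trend in intake as adaptation.

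This costs nothing in data collection. Its limit is that the rest weekday and Sunday are each seen once, so a Sunday difference cannot be separated from a late one.

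Moving the interviews so that each week recalls a Wednesday and a Sunday (days 3, 7, 10, 14) may look tidier but should not be adopted. Every session day would be a weekday and every non-session day a Sunday, so session status would be confounded with weekend and the only rest weekday would be lost. Under a linear slope the session-day artefact would also grow. The deviations are −5.5, −1.5, 1.5 and 5.5, with sum of squares 65, giving (−5.5 + 1.5) × 11/65 = −0.68 D over 11 days.

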#### Subjective hunger and satiety sensations

Subjective hunger and satiety sensations will be measured through the Visual Analog Scale (VAS) proposed by Flint et al. [34]. The VAS is composed of lines with a length of 100 mm, where the extremities express the minimum and the maximum of the individual’s perception of hunger and satiety, separately (Fig. 3). Subjects will be asked to make a mark on this line. The marked point corresponds to their feelings about hunger or satiety. This will be measured by the definition of the individual score [34]. The evaluation will be performed before and after the exercise sessions, as well as after the main meals (breakfast, lunch and dinner) on the days of food consumption assessments.

**Fig. 3 Fig3:**
[figure not shown]
Visual analog scale of hunger and satiety sensations

Prior to the first exercise session, an ad-libitum buffet will be provided to all experimental groups (vigorous, moderate and control).

Participants will be asked to record hunger and satiety sensations in a diary. In order to improve adherence, a text message will be sent to the participants reminding them to complete their diary.

#### Biochemical and hormonal analyses

Blood and salivary samples will be collected to investigate physiological mechanisms involved in energy expenditure (lactate and cortisol) and food consumption regulation (insulin, leptin and acylated ghrelin), at the first (baseline) and the 15th days of the intervention period, in the morning and after at least 10 h of fasting. Also, salivary cortisol and lactate will be measured after the first and last exercise sessions.

In order to measure salivary cortisol, fasting saliva sample will be collected about an hour after waking up and stored at 4 °C in the Salivette® tube, before eating and brushing the teeth. Participants will bring the salivary sample to the researchers in the same day. The Salivette® tubes will be centrifuged at 1000 × g for 3 min at room temperature and then stored at − 20 °C for later measures, by a commercial ELISA kit. To avoid any confounding factors, the participants will be advised to not do exercise and drink alcohol in the last 24 h, rinse their mouths with water through light mouthwashes immediately prior to collection.

Blood samples will be collected into a 6-ml EDTA K3 vacuum tube with Pefabloc®, 1 mg/mL of blood. The samples will be centrifuged at 3000 × g for 15 min at 4 °C. The serum samples will be aliquoted to identify Eppendorfs for future measurements of insulin, leptin and ghrelin, and stored at – 70 °C. The ghrelin aliquot will be acidified with HCl, to a final concentration of 0.05 N before storage.

Fasting glucose and lactate will be measured using a glucometer (Accu-Chek Active, Roche Diagnostics®, Mannheim, Germany) and a lactate analyzer (Lactate Plus, Nova Biomedical Corporation®, Waltham, MA, USA), respectively. Also, fasting insulin and leptin will be evaluated by a commercial RIA kit. On the other hand, measurements of ghrelin will be performed using a commercial ELISA kit.

The value of the Homeostasis Model Assessment of Insulin Resistance (HOMA-IR) index will be calculated by using the formula:(Fasting insulin (*μ*UI ⋅ mL) × fasting glucose (mmol ⋅ L^− 1^))/22.5 [35]

### Data analysis

Descriptive analysis for variables of interest consist of means and standard deviation for continuous variables and percentage for categorical variables.

Energy expenditure associated with physical activity will be assessed in the first hour of accelerometer usage, corresponding to the period of the exercise sessions, and over the course of 15 days. Differences between sessions for energy expenditure in the first hour will be performed by using a one-way analysis of variance (ANOVA), followed by a post-hoc Scheffé test. Differences in daily and accumulated physical activity energy expenditure between groups will be performed using linear mixed models that take into account the correlations between repeated measures over time and dropouts. The models will assess the rate of change of the outcomes by the treatment-by-time interaction variable. The covariance structure of the models will be tested and residuals analyses will be performed. To deal with the potential weartime differences between groups, sensitivity analysis will be performed and a “non-wear time” variable will be created and included in the model. Data analysis will be performed using SAS 9.3 (SAS Institute Inc, Cary, NC, USA). Statistical significance will be set at *p* < 0.05 for all analyses.

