Several physiological mechanisms, particularly hormonal, are involved in the energy expenditure and intake regulation and can explain these behavioral compensatory mechanisms [18, 19]. However, the existing interactions and the influence of physical exercise on these adjustments are still unclear. Therefore, it is necessary to better understand the relationship between physical exercise and energy expenditure, as well as the possible interdependence between energy expenditure and food consumption and the hormonal regulatory mechanisms related to energy balance in overweight individuals. The influence of different exercise intensities on energy expenditure and food intake should also be investigated. The EFECT study, which stands for “Physical Exercise and Compensatory Effects” in Portuguese, is designed to address this gap in the academic literature. For the main outcome, we hypothesize that a greater reduction on spontaneous physical activity energy expenditure will be observed in the vigorous exercise group (VEG) after the 15-day follow-up.

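### As worded, accelerometer wear starts with the first exercise session, so the primary outcome has no pre-exercise level, although a reduction is hypothesised and rate of change is tested

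*Protocol article*

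**What the plan says.** - **Hypothesis (Background):** by the end of the 15-day follow-up, "a greater reduction on spontaneous physical activity energy expenditure will be observed in the vigorous exercise group (VEG".
- **Start of wear (Data analysis):** expenditure is "assessed in the first hour of accelerometer usage, corresponding to the period of the exercise sessions", and also over the 15 days.
- **Sessions (Intervention and exercise protocol):** "exercise sessions in the evening (5–7 p.m.), performed three times a week (Monday, Wednesday and Friday) for 65 min, during a 2-week period".
- **Wear period (Physical activity energy expenditure):** "The device will be positioned at the anterior axillary line of the non-dominant hip, for 15 consecutive days". No run-in is described.
- **Valid days (same section):** "Non-wear time will be defined as ≥ 60 min of zero counts, with a minimum of 10 h constituting a valid day", and "individuals will have days excluded from the analysis if they failed to provide a minimum of 600 min (10 h) of valid data".
- **Day numbering (Food consumption):** the second day is a Tuesday, so day 1 is a Monday, which is an exercise day.
- **Analysis (Data analysis):** linear mixed models for daily and accumulated expenditure, with rate of change assessed by the treatment-by-time interaction.
- **Baselines that do exist:** biomarkers have a fasting sample on the morning of day 1, labelled baseline. Weight and body fat are measured for eligibility, and the treadmill test precedes the sessions.

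**The concern.** A reduction needs a level to be reduced from. Taken together, the sections on analysis, sessions, wear and day numbering place the first minute of accelerometry at the start of the first session. Every expenditure value is then recorded after the intervention has begun. The biomarkers have a baseline; the primary outcome has none.

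Three things are at stake:

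- A within-person fall cannot be estimated.
- A covariate likely to be strongly prognostic, the person's own habitual expenditure, is not collected.
- The treatment-by-time term sees only change after exercise started, so it can miss compensation that sets in at once and persists.

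The fitting day may also fail the trial's own valid-day rule, which would remove the evening after the first session from the daily data.

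**Working it through.** **1. The plan's own figure.** Inputs from Sample size: difference 110 kcal/day, SD 110 kcal, two-sided alpha 0.05, power 0.90, dropout 20%.

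n per arm = 2 × (1.960 + 1.282)² × (110/110)² = 21.01. Then 21.01/0.80 = 26.27, rounded up to 27, and 3 × 27 = 81. The stated size is reproduced. It is a calculation for a difference in mean level, not for a slope.

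**2. What the interaction can see.** Take the design effect of 110 kcal/day and fit a least-squares line to the between-group difference e(d) in daily expenditure over days d = 1 to 15: slope = Σ(d − 8)e(d) / Σ(d − 8)², with Σ(d − 8)² = 280. The shapes are assumptions.

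| Shape of the fall | Slope, kcal/day per day | Implied change over days 1–15 |
|---|---|---|
| Immediate and sustained, e = −110 | 0 | 0 |
| Settles early, e = −110(1 − exp(−d/2)) | −3.31 | −3.31 × 14 = −46 kcal |
| Linear, e = −110d/15 | −7.33 | −7.33 × 14 = −103 kcal |

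If day 1 is excluded, the early-settling fall shows as only −29 kcal over days 2–15. With day as a categorical factor, an immediate sustained fall still gives parallel profiles and no interaction.

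**3. The fitting day.** A 65-min session inside 5–7 p.m. starts between 17:00 and 17:55.

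- To midnight: 24:00 − 17:00 = 7.0 h, or 6.1 h from 17:55.
- To the 10 p.m. bedtime, if still sleep is scored as non-wear: 5.0 h, or 4.1 h.

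All are below 10 h, so on a calendar-day count the day is excluded in all arms. On 24-h blocks from fitting, the first block could pass: 5 h that evening plus 11 h from the 6 a.m. wake-up to 5 p.m. gives up to 16 h. It would still contain the session and follow the start of the intervention.

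**4. Value of a pre-exercise baseline for the mean comparison.** The documents give no correlation r between pre-exercise and on-study mean expenditure, so r is assumed. The variance ratio is 1 − r², the residual SD is 110 × √(1 − r²), and completers per arm are 27 × 0.8 = 21.6. The difference detectable with 90% power is SD × √(2/21.6) × 3.242.

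| r (assumed) | Variance cut | Detectable difference, kcal/day |
|---|---|---|
| none | 0 | 108.5 |
| 0.6 | 36% | 86.8 |
| 0.7 | 49% | 77.5 |
| 0.8 | 64% | 65.1 |

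**5. Biomarkers, two visits.** With equal variances, group-by-time compares changes, with variance proportional to 2(1 − r). Adjusting day 15 for day 1 gives 1 − r². The ratio is (1 + r)/2, a cut of (1 − r)/2, or 25% at an assumed r = 0.5.

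**The case against.** The strongest reply is that a randomised trial with a concurrent control needs no baseline for a valid comparison. The primary outcome is a two-week total, the sample size rests on a between-group mean difference, and the control arm supplies the reference level. This stands. A reader might infer that chance imbalance in habitual activity could pass for compensation and bias the result. The documents do not support that: such imbalance is ordinary random error, covered by the 5% test. Nor is a power shortfall shown, since 21.6 completers per arm give 90.8% power for the stated difference without adjustment.

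Further replies, and what remains of each:

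- **Stable person differences.** The mixed model's covariance absorbs these for a within-person slope. Correct, so the 36–64% applies only to a comparison of mean or total.
- **Accumulated expenditure.** If this is modelled as a running total, an immediate sustained fall accumulates as −110d, a slope difference of −110 kcal/day. The zero therefore applies to the daily outcome. The protocol does not say how accumulated expenditure enters the model.
- **Covariates.** An article may leave the covariate list to an analysis plan that is not shown, so its absence here is no error. An analysis plan cannot, however, supply accelerometry that was never collected.
- **Fitting time.** No sentence states it; it is inferred from the first-hour wording. The SPIRIT figure is not shown. If it lists earlier wear, the Data analysis wording contradicts it and needs correcting.
- **Loss of day 1.** This depends on calendar days, falls alike on all arms and leaves 14 days. The first session still enters the separate first-hour ANOVA.

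**Conclusion.** The point holds in limited form. As the protocol is worded, no pre-exercise activity level is collected for the primary outcome, yet a reduction is hypothesised and rate of change is the quantity tested. The treatment-by-time test on daily expenditure has no sensitivity to an immediate, sustained fall of the design size and recovers less than half of one that settles within a few days (46 of 110 kcal, under the assumed shape).

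It would be wrong to conclude that the primary comparison is invalid: the between-group difference in the two-week total or mean is unbiased. The loss is in interpretation and precision. The size of the precision loss depends on an assumed correlation. Exclusion of the fitting day is conditional on calendar-day counting. The plan should be changed on this point, but the trial's validity does not hang on it.

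**What to change.** **(a) Analysis wording, all participants.** Base the primary inference on the between-group difference in mean or total spontaneous expenditure, adjusted for body weight or fat-free mass and VO2peak, and word the hypothesis as that difference. The treatment-by-time term can stay as a secondary description of time course. Analyse each biomarker at day 15 adjusted for its day-1 value, in place of group-by-time. These covariates are already measured before exercise, so the cost is wording only. The documents give no basis for sizing the gain from weight and VO2peak.

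**(b) Participants still to be recruited.** Fit the same device for some full days before the first session and use mean daily expenditure from that period as a covariate, with a missing-baseline indicator for those already enrolled. The cost is a minor amendment, extra wear days and a partly missing covariate. The setting is the 2017 school year and recruitment was under way at publication in March 2018, so few participants may benefit; (a) should not depend on (b).

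**(c) Definitions.** State when the device is fitted and whether a day for the 10-h rule is a calendar day or a 24-h block from fitting. This costs two sentences.
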